**Fig. 1 Fig1:**
[figure not shown]
Consort flow chart for enrolment and follow-up plan for randomized controlled trial

### Intervention package

The intervention development and evaluation followed the Medical Research Council (MRC) guidelines. The key element of development and evaluation process as per guidelines, i.e., (1) development, (2) feasibility/piloting, (3) implementation, and (4) evaluation, not following a linear sequence, was followed for the current study. Thereafter, the intervention package development, validation, and feasibility assessment was tested before implementing and evaluating its effectiveness in the current study (Fig. 2).

**Fig. 2 Fig2:**
[figure not shown]
Steps of development and validation of intervention package

#### Intervention/treatment arm

*✓ Arm 1: Brief intervention* Face to face counseling, motivational videos, and information leaflet will be included.*✓ Arm 2: Intensive intervention* A brief intervention intended to enhance self-efficacy and motivation for quitting will be supported with other modalities in the intensive intervention arm. The supportive modalities including text messages and telephone counseling will enforce the chances of maintaining abstinence. Besides, information to support family and friends during quitting process, tips including coping with cravings, avoiding triggers, and distracting one’s mind from tobacco use will also be included.

The details of the intervention provided in arm 1 (brief intervention) and arm 2 (intensive intervention) are given in Table 1.

**Table 1 Tab1:** Details of behavior change intervention package in two arms (brief intervention arm and intensive intervention arm) of the study

***Intervention arm***	***Mode and content of delivery***	***Time duration/frequency/provider***	***Benefits***
**Brief and intensive**	(Individual counseling) This will involve face-to-face appointments of patient with researcher aimed to motivate, guide, and psychologically assist tobacco users in quitting. This patient-centered approach enhances an individual’s motivation for change through self-examination and identification of ambivalence to change and the subsequent resolution leading to sustained positive behavior change. It will include asking patients about their tobacco use status, and discuss the options that exist to support a quit attempt	10–20 min/once during first contact/researcher	Both minimal (< 20 min in 1 visit) and intensive (≥ 20 min plus > 1 follow-up visit) physician-advice interventions effectively increase the proportion of adults who successfully quit tobacco and remain abstinent for ≥ 6 months [8]. There is a dose–response relationship between the intensity of counseling and cessation rates (i.e., more or longer sessions improve cessation rates) [38]
	(Motivational videos) Videos based on real life stories of patients with tobacco use history will educate and sensitize patients and care givers on harmful effects of tobacco and motivate patients to quit	3–5 min/once during first contact/researcher	Technology including mobile phones, the internet, and social media platforms, can increase access to care by extending the work of counselors and overcoming the geographical barriers. These supports can increase the likelihood of adults quitting compared with no intervention and can be a cost-effective adjunct to other treatments [39]
	(Patient information leaflet (PIL)) Patient information leaflet will be based on specific characteristics or concerns of tobacco users and include written material aiming to educate patients about the disease, ill effects of using tobacco on health, benefits of quitting and how to resist cravings and avoid relapse	Once at first contact/researcher	Providing self-help materials (primarily print-based) tailored to the individual patient (that is, beyond a brochure that simply describes the health effects of tobacco use and benefits of cessation) is effective in improving tobacco abstinence [40]
**Intensive**	(Telephone counseling) Counseling through regular telephone follow-up will provide support and encouragement to individuals who uses tobacco and want to quit or individuals who have recently quit	05–15 min/five times at < 1, 4, 6, 9, and 12 weeks in 3 months after enrolment/researcher	Telephone-based access to counseling and smoking cessation resources increases cessation rates. The majority of helplines provide access to individual counseling; the greatest amount of counselor contact, the greater the likelihood of successful cessation [41]
	(Text messages using SMS) Messages will include short text based on the current stage of behavior as per trans-theoretical model for their motivation and support regarding tobacco cessation and maintaining quit status	Bi-weekly for 3 months/researcher	Technology, including mobile phones, the internet, and social media platforms, has the power to increase access to care by extending the work of counselors and overcoming geographical barriers. These supports can increase the likelihood of adults quitting compared with no intervention and can be a cost-effective adjunct to other treatments [39]

The intervention to be delivered was adapted by collecting data from stakeholders, including health professionals, and interviewing tobacco users from the setting.

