**Methods/design:**

A two-arm randomized controlled trial (RCT) in a tertiary healthcare hospital will be performed. A total of 360 tobacco users attending NCD clinics in four departments, cardiology, neurology, pulmonary medicine, and ENT (otolaryngology), will be recruited over a period of 3 months. After ascertaining the eligibility criteria, they will be followed up to 6 months (1, 3, 6) for their tobacco use status, readiness to quit, nicotine dependence, stage of behavior change, and self-reported and biochemical validation (urine cotinine) for tobacco abstinence. Assignment of intervention including allocation concealment, sequence generation, and blinding will be done as per SPIRIT guidelines for RCT protocols.

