### Inclusion, exclusion, and dropout/withdrawal criteria

Participants will be eligible provided they (1) are above 18 years of age, (2) have a history of using tobacco for the last 1 month and at least 10 pack-year or equivalent tobacco, (3) can read and understand English, Hindi, or Punjabi, (4) have a mobile phone with text messages/WhatsApp messages accessibility, and (5) are willing to quit and provide written consent for intervention and follow-up of 6 months in the study.

Participants will be excluded if they (1) are unable to understand any of the languages as mentioned above, (2) are severely ill to participate in the study and require urgent attention for any of the medical problems, (3) are already taking treatment for tobacco cessation, and (4) are mentally ill to accord informed consent for the study.

Participants will be discontinued for the study if they (1) voluntarily withdraw the consent, (2) are not complying with the study schedule, and (3) are not in a condition to continue with the study due to migration or other reasons. The reason for withdrawal will be collected, and no more follow-up will be initiated. Participants who drop out of the study will be considered tobacco users.

Intention-to-treat will be used for data analysis, wherein all participants who are randomized to a treatment arm and receive their assigned intervention are included in the final analysis whether they complete the study or respond to follow-up surveys at study end points. This method will be used to avoid any bias that can potentially arise because of crossover and dropouts, affecting the initial random assignment to treatment groups.

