### Sample size

Based on existing literature [37], with a success rate in brief (p1) and intensive (p1) intervention arm of 16.8% and (p2) 30.3% respectively, we expected a difference of approximately 13.5% in cessation rates between the two groups. Sample size was calculated using the Sealed Envelope Ltd. 2012 software application. Power calculator for binary outcome superiority trial based on the formula *n* = *f*(α/2, *β*) × [*p*1 × (100 − *p*1) + *p*2 × (100 − *p*2)]/(*p*2 − *p*1)2 and *f*(*α*, *β*) = [*Φ*-1(*α*) + *Φ*-1(*β*)]2, where *Φ*-1 is the cumulative distribution function of a standardized normal deviate. The alpha level (*α*) at 0.05 and power (*β*) 80% was set to detect a clinically significant difference between the two arms. Sample size was inflated using 20% dropout rate making a total sample size of 366. Participants will be randomly assigned into two arms at a ratio of 1:1 with 183 in each arm. The planned sample size will be recruited in approximately 3 months and followed up for 6 months.

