### Data analysis

Data analysis will be undertaken by the investigators using the SPSS statistical analysis package.

Analysis of primary outcome of 7-day point prevalence tobacco abstinence at 6 months will be based on an intention-to-treat approach. It shall be done by estimating the mean difference in percentage of quit rates between the intensive and brief intervention groups at 6 months.

Regression analysis and /or ANOVA will be used for primary and secondary outcomes. For not normally distributed data, robust standard errors, truncation, or transformation will be used. For missing data, multiple imputations will be used. The net changes in primary and secondary outcome measures will be considered by exploratory analysis. Marginal means and treatment effect with its associated 95% CI and probability values will be presented and reported. The conventional significance level of 0.05 will be used in all analyses to reject the null hypothesis of no difference between two groups.

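### Only the intensive arm gets calls and texts to month 3, and dropouts count as tobacco users, so any difference in retention would bias the 6-month comparison towards the better-retained arm

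*Protocol article*

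**What the plan says.** **Contact.** Table 1 gives both arms one counselling session, videos and a leaflet at first contact. For the brief arm that is the whole package: "Face to face counseling, motivational videos, and information leaflet will be included". The intensive arm adds telephone counselling, "five times at < 1, 4, 6, 9, and 12 weeks in 3 months after enrolment/researcher", and text messages, "Bi-weekly for 3 months/researcher". The assessment schedule is common to both arms; the abstract says "they will be followed up to 6 months (1, 3, 6) for their tobacco use status".

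**Dropouts.** The section on inclusion, exclusion and dropout says "Participants who drop out of the study will be considered tobacco users" and, of those who withdraw or are discontinued, "The reason for withdrawal will be collected, and no more follow-up will be initiated". The Data analysis section says "For missing data, multiple imputations will be used" and does not say how this fits with the first rule.

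**Primary comparison.** It is the difference in quit percentages between arms at 6 months, by intention to treat.

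**Planned dropout.** "Sample size was inflated using 20% dropout rate" is a single overall figure. The limitations paragraph of the Discussion accepts that data will be missing but does not consider a difference between arms.

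**The concern.** Scoring dropouts as users is often regarded as conservative. For a difference between arms, that is safe only if both arms lose the same share of participants or if everyone lost is using tobacco. Here the treatment under test is itself additional contact, made by the researcher who also assesses the outcome. Regular calls and texts may keep people in the study as well as help them quit. A brief-arm participant who has quit but is lost would be counted as a failure, while a comparable intensive-arm participant who stays in touch would be counted as a success. The primary estimate would then mix an effect on tobacco use with an effect on who returns at 6 months, and the nominal 0.05 level would not hold.

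**Working it through.** **Reproducing the plan's figure.** Inputs from the Sample size section: 16.8% and 30.3%, two-sided alpha 0.05, power 80%.

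n = (1.960 + 0.842)² × [0.168 × 0.832 + 0.303 × 0.697] / 0.135² = 151.15, rounded up to 152 per arm. Then 152 × 1.2 = 182.4, rounded up to 183 per arm, or 366 in total. This matches the plan. The 20% enters once, as a common rate.

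**Formula for the bias.** With dropouts scored as users, the observed rate is the true rate × (1 − dropout in that arm). With no true effect, the false difference is the retention gap × the abstinence rate among the extra participants lost.

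**Assumptions.** The same true abstinence in both arms, dropouts as likely to be abstinent as completers, 183 per arm, and a two-sided pooled z-test by normal approximation. Every dropout split below is assumed; each averages the plan's 20%.

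| True rate, both arms | Dropout brief / intensive | Observed brief / intensive | False difference | Two-sided type I error |
|---|---|---|---|---|
| 16.8% | 20% / 20% | 13.4% / 13.4% | 0 | 5.0% |
| 16.8% | 25% / 15% | 12.6% / 14.3% | +1.7 | 7.6% |
| 16.8% | 30% / 10% | 11.8% / 15.1% | +3.4 | 15.6% |
| 30.3% | 25% / 15% | 22.7% / 25.8% | +3.0 | 10.4% |
| 30.3% | 30% / 10% | 21.2% / 27.3% | +6.1 | 27.2% |
| 16.8% | 15% / 25% | 14.3% / 12.6% | −1.7 | 7.6%, mostly favouring brief |

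Second row in full: 0.168 × 0.75 = 0.1260 and 0.168 × 0.85 = 0.1428, a difference of 0.0168. The standard error is √(2 × 0.1344 × 0.8656 / 183) = 0.0357, so z shifts by 0.47. The chance of a false significant result is 6.8% favouring intensive plus 0.75% favouring brief, about 7.6%.

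**Abstinence among those lost**, for a 10-point gap at 16.8%:
- As likely to be abstinent as completers: 0.10 × 16.8 = 1.7 points.
- Half as likely: 0.10 × 8.4 = 0.8 points.
- None abstinent: 0.

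**Checking a possible sensitivity analysis.** Giving only brief-arm dropouts their completers' quit rate does not work. With equal 20% dropout and no true effect it gives 16.8% against 13.4%, a false −3.4 points where there was no bias. Giving dropouts in both arms their own arm's completer rate returns 16.8% against 16.8%. At 25% / 15% that symmetric version also returns a zero difference.

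**The case against.** The strongest objection is that unequal retention is an inference. The article gives no dropout by arm, and the splits above are illustrations. That stands, so the point can only be conditional.

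The contrast in contact is also narrower than it first looks. Both arms share the 1-, 3- and 6-month assessments, the week 4 and week 12 calls fall close to two of them, and Table 1 schedules no extra contact in either arm for the 3 months before the endpoint. This may shrink the gap. It need not close it, because participants who withdraw or are discontinued before month 3 are not followed further.

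A reader might infer that the bias must favour the intensive arm. The documents do not support that. Participants can be discontinued for not keeping to the study schedule. If missed calls count, the intensive arm has more ways to lose people and the sign reverses.

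A reader might also infer that the true type I error exceeds 0.05. That follows only if retention differs, some dropouts are abstinent, and dropouts are scored as users in the primary analysis. If multiple imputation governs instead, the bias largely does not arise.

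Finally, Table 1 describes intervention content. The article's silence on reminders and tracing does not show that the full protocol lacks them, and no such omission is alleged. The extra contact is the treatment being tested and is not itself a fault.

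**Conclusion.** The point holds in conditional form. Two stated choices interact: contact that differs by arm up to month 3, and scoring dropouts as users in a comparison of quit percentages. If retention differs and some dropouts are abstinent, the primary difference is biased towards the better-retained arm.

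For an assumed 10-point gap the false difference is +0.8 to +1.7 points at 16.8% abstinence, depending on whether the extra dropouts are half or fully as likely to be abstinent as completers. It reaches +3.0 points if the common rate is 30.3%. Against the planned 13.5 points this is modest. It could inflate an estimate or turn a borderline result significant, but a gap of this size would not by itself produce the planned effect. A reading that a positive trial would merely reflect retention goes beyond the documents. So does any firm statement of direction.

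Whether the problem arises at all depends first on which missing-data rule governs the primary outcome, and the article leaves that unresolved.

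**What to change.** 1. Reconcile the dropout rule in the withdrawal criteria with the multiple imputation under Data analysis, and name the one that governs the primary outcome.
2. In the follow-up procedures, state the same neutral reminder, without cessation content, before each 1-, 3- and 6-month assessment in both arms, and the same fixed number of tracing attempts after a missed one. If the full protocol already has this, confirm that it applies equally to both arms.
3. Report dropout by arm.
4. Next to the primary result, show a symmetric sensitivity analysis that varies abstinence among dropouts in both arms, from zero up to that arm's completer rate. Do not impute the brief arm alone.

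The cost is about three short reminders per participant, to phones that eligibility already requires, a little more researcher time, and slightly more contact in the brief arm. The intervention content of both arms is unchanged. The article describes recruitment as ongoing, so the second item can reach only the follow-up that remains. The other three can be settled before analysis.

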### Data collection

After fulfilling the inclusion criteria and seeking written consent, the researcher will collect data from tobacco users enrolled in the study. Baseline and end of follow-up (6 months) of intervention assessment will include assessment of tobacco use (daily tobacco consumption, age of initiation, quit attempt, treatment sought for cessation (if any)); knowledge, attitude, and practices about tobacco use.

The assessment of motivation to quit tobacco will be undertaken using Readiness to Change questionnaire [42] (RCQ), nicotine dependence using FTND scale [43], and stages of behavior change using a trans-theoretical model of behavior change at each follow-up (0, 1, 3, 6) months. The self-reporting assessment for 7-day point prevalence and continuous tobacco abstinence will also be done at each (0, 1, 3, 6) follow-up month. In addition, a urine sample will be collected at the last follow-up (6 months of intervention) to confirm the cotinine presence biochemically (Table 2).

**Table 2 Tab2:**
[figure not shown]
Data collection items and schedule at baseline and follow-up in the study

^***^Readiness to change questionnaire

^**^*FTND* Fagerstrom Tobacco Nicotine Dependence

^*****^*7DPPA* Seven-day point prevalence abstinence

T0: baseline, T1: 1 month follow-up, T2: 3 months follow-up, T3: 6 months follow-up

Sample handling: Urine sample will be collected in container with a lid to prevent leakage and then transported from the collection to storage site using dry ice in an ice box. At the storage site, the collected sample will be stored in refrigerator maintained at − 80° temperature with back-up generator system to provide power during an electrical outage. Proper labeling to withstand the storage condition, i.e., good label material will be used to have readable printing even after long-term storage. After performing testing procedure and analysis, the samples will be discarded after mixing with sodium hypochlorite solution. Biological waste management guidelines followed in the institute (PGIMER Chandigarh) and biological sample collection, processing, storage, and information management details provided in the reference will be followed for sample handling during the study [44].

### Outcome measures

#### Primary outcome

Validated 7-day point prevalence tobacco abstinence at 6 months (last follow-up) measurement using urinary cotinine

#### Secondary outcomes

Measures at each follow-up period 1, 3, and 6 months:Self-reported continuous tobacco abstinenceSelf-reported 7-day point prevalence tobacco abstinenceSelf-reported tobacco use reductionReadiness to change by RCQScores of Nicotine dependence by FTND instrumentNumber of quit attempts and relapses at each follow-up

Measures at follow-up 6 months:Change in knowledge, attitude, and practices score at 6 months (Table 3)

**Table 3 Tab3:** Study outcome measures at different time intervals

**Outcomes**	**Domain**	**Specific measurement**	**Specific metric**	**Method of aggregation**	**Time points**
*Validated 7-day PPA*	Abstinence status	Cotinine (biochemically)	Abstinence	Proportion	6 months
*Self-reported CA*	Abstinence status	Self-reported	Abstinence	Proportion	1, 3, 6 months
*Self-reported 7DPPA*	Abstinence status	Self-reported	Abstinence	Proportion	1, 3, 6 months
*Knowledge, attitude, and practices (KAP)*	Knowledge, attitude, and practices	Questionnaire	Change from baseline	Mean	6 months
*Nicotine dependence*	Dependence score	FTND	Change from baseline	Mean	1, 3, 6 months
*Quit attempts*	Quit attempts	Follow-up questionnaire	Presence of quit attempts	Number of quit attempts	1,3, 6 months
*Readiness to change*	Stage of behavior change	Readiness to change questionnaire	Change in stage from baseline	Proportion	1,3, 6 months
*Reduction in tobacco use*	Reduction tobacco use	Quantity	Change from baseline	Proportion	1, 3, 6 months

### Data analysis

Data analysis will be undertaken by the investigators using the SPSS statistical analysis package.

Analysis of primary outcome of 7-day point prevalence tobacco abstinence at 6 months will be based on an intention-to-treat approach. It shall be done by estimating the mean difference in percentage of quit rates between the intensive and brief intervention groups at 6 months.

Regression analysis and /or ANOVA will be used for primary and secondary outcomes. For not normally distributed data, robust standard errors, truncation, or transformation will be used. For missing data, multiple imputations will be used. The net changes in primary and secondary outcome measures will be considered by exploratory analysis. Marginal means and treatment effect with its associated 95% CI and probability values will be presented and reported. The conventional significance level of 0.05 will be used in all analyses to reject the null hypothesis of no difference between two groups.

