#### Sequence generation

The participants meeting the inclusion criteria will be randomly assigned by the researcher to either control or intervention arm with a 1:1 allocation as per the randomization sequence generated in advance by a computer program. To ensure a balanced representation of the participants in two groups from various departments, stratified block randomization will be used.

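### Randomisation is stratified by department, but the stated primary analysis is a simple difference in quit rates with an open choice of model and no mention of department

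*Protocol article*

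**What the plan says.** Protocol article, Sequence generation: "To ensure a balanced representation of the participants in two groups from various departments, stratified block randomization will be used". The stratum is not labelled in so many words, but the stated purpose makes it department. Study design and setting names four: cardiology, pulmonary medicine, neurology and ENT.

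Protocol article, Data analysis: the primary outcome, cotinine-validated 7-day abstinence at 6 months, is to be analysed by "estimating the mean difference in percentage of quit rates between the intensive and brief intervention groups at 6 months". The section continues: "Regression analysis and /or ANOVA will be used for primary and secondary outcomes". It then lists remedies for data that are not normally distributed, and promises marginal means and a treatment effect with 95% CI and p-values. Neither department nor any other covariate is named.

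Protocol article, Sample size: the calculation is a two-proportion comparison without a stratum term, "with a success rate in brief (p1) and intensive (p1) intervention arm of 16.8% and (p2) 30.3% respectively".

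**The concern.** Stratified blocks make the arms nearly equal within each department, so differences in quitting between departments contribute almost nothing to the chance variation in the treatment contrast. A plain two-sample standard error still counts that variation as noise. If departments differ, the interval is wider than it need be and the test runs below its nominal 5%.

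The second part is the open method. For one yes/no outcome the text allows a difference in percentages, an unspecified regression, ANOVA, or a combination. These can give different p-values, and nothing says which one decides the trial. This matters more here because the trial is open-label, the outcome assessor knows the allocation, and the investigators run the analysis themselves.

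**Working it through.** **Inputs from the protocol article.** Quit rates 16.8% (brief) and 30.3% (intensive); two-sided 5% level ("The conventional significance level of 0.05 will be used in all analyses", and the printed formula uses α/2); 80% power; 183 per arm; four departments.

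**Step 1: the plan's own figure.** Its formula gives n = (1.960 + 0.842)² × [0.168×0.832 + 0.303×0.697] / 0.135² = 7.849 × 0.350967 / 0.018225 = 151.15, so 152 per arm. Then 152 × 1.2 = 182.4, so 183 per arm and 366 in total. This matches the document ("Sample size was inflated using 20% dropout rate making a total sample size of 366").

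**Step 2: standard error with and without strata.** Let department rates be the planned rates plus a shift that is the same in both arms and averages zero, and let V be the variance of the shifts over four near-equal departments. The average of (p+s)(1−p−s) over departments is p(1−p) − V. Hence:

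- unadjusted SE = √{[p₁(1−p₁) + p₂(1−p₂)] / n}
- stratified SE = √{[p₁(1−p₁) + p₂(1−p₂) − 2V] / n}

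Example with shifts −15, −5, +5, +15 points: V = (2×0.0225 + 2×0.0025)/4 = 0.0125. The unadjusted SE is √(0.350967/183) = 0.0438. The stratified SE is √((0.350967 − 0.025)/183) = √(0.325967/183) = 0.0422. The ratio is √(0.350967/0.325967) = 1.038.

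**Step 3: level and power.** These were simulated with 200,000 runs per scenario and 46, 46, 46 and 45 participants per department and arm. The null rate was (16.8 + 30.3)/2 = 23.55% in both arms. The shifts are **assumptions**; the documents give none.

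| Assumed shifts (points) | V | SE ratio, unadjusted / stratified | Level, unadjusted | Level, stratified | Power, unadjusted | Power, stratified |
|---|---|---|---|---|---|---|
| none | 0 | 1.000 | 5.1% | 5.2% | 86.8% | 87.0% |
| −5, −2, +2, +5 | 0.00145 | 1.004 | 5.0% | 5.2% | 86.8% | 87.2% |
| −10, −4, +4, +10 | 0.0058 | 1.017 | 4.7% | 5.2% | 87.2% | 88.1% |
| −15, −5, +5, +15 | 0.0125 | 1.038 | 4.3% | 5.3% | 87.6% | 89.3% |

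Check on the last row: under the null p(1−p) = 0.2355 × 0.7645 = 0.1800, the SE ratio is √(0.1800/0.1675) = 1.037, and 2 × [1 − Φ(1.96 × 1.037)] is about 4.2%, in line with the simulated 4.3%.

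**Two cautions.** The power columns assume that all 183 per arm are analysed at the planned rates. The stratified test runs slightly above 5%, so a small part of the power gap (0.2 points even without department differences) comes from that and not from the strata. The simulation used a department-weighted difference in proportions, not a fitted logistic model.

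**The case against.** **Department is omitted, not excluded.** The section never calls the analysis unadjusted, it allows regression, and marginal means are compatible with an adjusted model. A covariate list is often left to a full protocol or analysis plan, which is not shown. This stands, and a reader should not infer that the investigators decided to ignore the strata. What remains is what the article does fix: a plain between-arm difference, beside a choice of methods that does not settle the primary test.

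**The harm is conditional and small.** This also stands. Without department differences the loss is nil, and the error is on the conservative side. The stated purpose of stratifying was balance, not precision.

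**ANOVA and the non-normality remedies may be meant for other outcomes.** The sentence covers primary and secondary outcomes together, and the secondary ones include mean changes in FTND and in the knowledge, attitude and practices score. For a binary outcome with two arms, a linear model's arm coefficient is exactly the difference in proportions, and robust standard errors are among the listed tools. The text is therefore loose rather than unworkable, but it should say which tool goes with which outcome.

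**A reader might infer that the lost precision falls on a trial already below its stated power.** The documents do not establish that. By the plan's formula, power is about 87% with all 183 per arm at the planned rates: 0.135/0.0438 − 1.96 ≈ 1.12. It is about 79% if 20% are lost and left out (146.4 per arm), and about 76% if 20% drop out and count as users on top of the planned rates (13.4% versus 24.2%). The article does not say whether its assumed rates already count dropouts as users.

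**Conclusion.** The point holds as a modest one. The design stratifies by department, the stated primary estimator does not carry the strata, and the primary model is left open. Under assumed department shifts of 0 to ±15 points, ignoring department makes the standard error about 0 to 4% too wide, lowers the actual level to about 4.3% at most, and costs up to about 1.7 points of power. Type I error is not inflated.

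The range rests on near-equal departments, shifts common to both arms, and full follow-up. A wider spread gives more: department rates of 5, 15, 30 and 44% would make the SE 6.7% too wide and the level 3.6%. Nothing in the documents supports a 39-point gap between departments, so that should not be read as the expected size.

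The absence of baseline FTND from the analysis is not an error. Randomisation is not described as stratified on it, and adjusting for it is an optional gain.

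**What to change.** In the Data analysis section, name one primary analysis. For example: logistic regression of cotinine-validated abstinence at 6 months on arm and department, with the marginal (standardised) risk difference, its 95% CI and p-value as the primary result. This keeps the quantity that the article already names. Present the unadjusted difference in quit rates as supportive. Restrict ANOVA and the remedies for non-normal data to the continuous secondary outcomes. Baseline FTND may be added as a covariate if it is specified in advance.

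The cost is wording. Department must be known to randomise, FTND is collected at month 0, and the sample size does not change. Recruitment is under way, so the choice should be recorded before outcome data are analysed.

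### FTND and KAP are set as mean change from baseline with no baseline covariate named, and undefined truncation is allowed for non-normal data; baseline-adjusted regression on all recorded values would be better for these secondary outcomes

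*Protocol article*

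**What the plan says.** Under Secondary outcomes, Table 3 gives the metric for KAP, FTND and reduction in tobacco use as "Change from baseline". KAP and FTND are aggregated as means and tobacco reduction as a proportion. The outcome list repeats the KAP measure as "Change in knowledge, attitude, and practices score at 6 months".

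Under Data analysis, the model is stated in one sentence: "Regression analysis and /or ANOVA will be used for primary and secondary outcomes". No covariate is named and none is excluded. The next sentence reads: "For not normally distributed data, robust standard errors, truncation, or transformation will be used". Truncation is not defined, no cut-off is given, and nothing says which of the three remedies applies when. The same section also states: "The net changes in primary and secondary outcome measures will be considered by exploratory analysis".

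Three other places bear on the point. The Data collection section has FTND, KAP and daily consumption recorded at baseline. Sequence generation describes stratified block randomisation to balance the arms across departments. The section on inclusion, exclusion and dropout commits to intention-to-treat, keeping in the final analysis everyone who was randomised and received the assigned intervention.

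**The concern.** There are two separate issues.

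First, an ANOVA of change scores without the baseline value is a permitted reading of the plan. It is less precise than an analysis that adjusts for baseline, and the baseline values are already collected.

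Second, the three remedies for non-normal data are not equivalent. Robust standard errors keep every participant and leave the estimate unchanged. Truncation, read as trimming, removes participants because of their outcome. On a consumption measure the largest falls belong largely to heavy users who quit, so trimming that tail discards part of the effect under study. It also conflicts with the intention-to-treat commitment. Non-normal consumption data are to be expected, because the sample-size section assumes that 16.8% and 30.3% will stop, and those who stop use nothing. The choice of remedy would fall to investigators in an open-label trial, after they have seen the data.

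At stake are the precision and size of the secondary treatment effects.

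**Working it through.** **The plan's own figure.** The article's only sample-size figure is for the binary primary outcome. With (1.960 + 0.842)² = 7.849, n = 7.849 × (0.168 × 0.832 + 0.303 × 0.697) / 0.135² = 151.1, rounded up to 152 per arm. Then 152 × 1.2 = 182.4, so 183 per arm and 366 in total, as stated. This figure does not depend on how the scores are analysed. The article gives no SD, correlation or power for FTND, KAP or consumption.

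**Precision of the change score.** Assume equal SDs at baseline and follow-up, and correlation r. The variance of the arm difference is proportional to 2(1 − r) for an unadjusted change score and to 1 − r² for a baseline-adjusted analysis. The ratio of adjusted to unadjusted is (1 + r)/2.

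| r (assumed) | (1 + r)/2 | Excess variance, unadjusted | Excess SE | 366 unadjusted is worth, adjusted |
|---|---|---|---|---|
| 0.3 | 0.65 | 1/0.65 = 1.54, so 54% | 24% | 238 |
| 0.5 | 0.75 | 1/0.75 = 1.33, so 33% | 15% | 274 |
| 0.7 | 0.85 | 1/0.85 = 1.18, so 18% | 8.5% | 311 |

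If the change score is regressed on arm and baseline, the treatment coefficient is identical to that from regressing the follow-up value on arm and baseline. The loss therefore arises only if baseline is left out of the model.

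**Effect of truncation.** This was simulated for mean consumption, with 183 per arm and 2,000 runs per setting. From the article: quit rates of 16.8% and 30.3%. Assumed: log-normal baseline use with median 15 units/day and log-scale SD 0.5; quitters at zero; continuing users in both arms at a median of 12 units/day with the same log-scale SD. Here ρ is the correlation of log use among continuing users.

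| ρ | Effect, all data | Lowest 5% trimmed | Capped at 5th/95th percentile | Quitters among those trimmed |
|---|---|---|---|---|
| 0.3 | −1.816 | −1.417 (22% smaller) | −1.640 (10% smaller) | 65% |
| 0.5 | −1.835 | −1.354 (26% smaller) | −1.628 (11% smaller) | 73% |
| 0.7 | −1.832 | −1.275 (30% smaller) | −1.614 (12% smaller) | 83% |

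Quitters are (16.8 + 30.3)/2 ≈ 23.6% of all simulated participants, so trimming selects them heavily. Power runs from 34% to 49% with all data, 29% to 37% after trimming and 37% to 53% after capping.

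**Effect of transformation, same model.** A plain log is undefined at zero. If zeros are dropped, all quitters go and the effect is 0 (5% rejection), because continuing users were given equal use in both arms. With log(1 + x) everyone is kept and power is 79% to 84%.

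**The case against.** Much can be said for the plan as it stands.

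- Change from baseline is a metric, not a model. Regression is planned and a baseline covariate is not excluded. A statistical analysis plan that is not shown may name one, and then nothing is lost. This stands and makes the precision loss conditional.
- Robust standard errors are listed first among the three remedies. This stands too: the plan already contains the remedy recommended here.
- Table 3 summarises tobacco reduction as a proportion, so a difference in mean units per day is not its stated summary. The argument from mean change therefore applies directly to FTND and KAP, and to consumption only if it is analysed as continuous. KAP has no stated zero point for quitters, so the pile-up at zero does not carry over to it.
- Truncation may mean capping, which removes nobody and slightly raised power in the simulation. A transformation that keeps zeros did better still. A blanket ban on transformation would be a preference about scale, not the correction of an error.
- The primary outcome is "Validated 7-day point prevalence tobacco abstinence at 6 months (last follow-up) measurement using urinary cotinine", which is binary, and net changes are labelled exploratory.

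A reader might infer that the plan will remove the quitters and erase the effect. The article does not support that: only dropping every zero, for example by a plain log, gives an effect of about 0, and the article does not state such a rule. A reader might also infer a certain loss of a third or more in precision, but that requires both an omitted baseline and a low correlation.

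These points narrow the concern without removing it. The article itself lists truncation as permitted, and trimming is one ordinary meaning of the word. Unadjusted ANOVA of change is also within its terms.

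**Conclusion.** The point holds as an improvement to the secondary analyses. For FTND and KAP, an unadjusted comparison of change scores would carry 18% to 54% more variance than a baseline-adjusted one, for an assumed r of 0.7 down to 0.3 and equal SDs at the two times. For a continuous consumption measure, trimming the lowest 5% of change would shrink the effect by about 22–30%, and capping by about 10–12%; both ranges rest on the assumed consumption model. Neither loss is certain, since baseline adjustment is not excluded and truncation is undefined. The primary outcome and the sample size are untouched. Adjustment for baseline uses data already collected, and no reason is given for allowing an outcome-based removal rule that conflicts with the intention-to-treat statement.

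**What to change.** In the Data analysis section, state that FTND and KAP, and tobacco quantity if it is analysed as a continuous measure, will be compared by regression of the follow-up value on arm, baseline value and department (the apparent randomisation stratum). All participants stay at their recorded values, with quitters at zero consumption, and heteroscedasticity-robust standard errors are the primary remedy for non-normality. Delete truncation. Keep a transformation only as a prespecified sensitivity analysis in a form that retains zeros, such as log(1 + x). Table 3 can still report mean change descriptively.

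The cost is a few lines of analysis wording. No new data, visits or participants are needed.
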